### Measures

#### Primary Outcomes: Cancer Risk Behavior Outcome Measures

We will use validated self-report measures of each cancer risk behavior in the T_0_-T_5_ surveys presented in Table 1.

**Table 1 table1:** Primary and secondary cancer risk behavior outcome measures.

Cancer risk behavior	Measure	Metric
Physical activity	Primary and secondary: Global Physical Activity Questionnaire [146]	Minutes per week of MVPA^a^ (primary) Meet 150 minutes per week goal (secondary)
Diet	Primary: Dietary Screener Questionnaire [147,148] Secondary: other meal behaviors [149-152]	Intake per day of fruits, vegetables, whole grains or fiber, added sugars (from sugar-sweetened beverages), and red or processed meats Frequency of eating meals and snacks, fast food, and skipping meals
Nicotine product use	Primary: 30-day prolonged tobacco or nicotine product abstinence [153] Secondary: 7-day point prevalence of smoking [153] Secondary: readiness to quit [154]	Use in the past 30 days (every day, some days, and not at all) Use in the past 7 days (every day, some days, and not at all) 10-point rating (1=no thought of quitting and 10=taking action to quit)
Alcohol intake	Primary: consumption of alcoholic drinks [155] Secondary: binge drinking (male individuals: 5 drinks per sitting and female individuals: 3 drinks per sitting)	Number of days in the past 30 days; number of drinks per occasion Number of times in the past 30 days
UV exposure	Primary: sunburn prevalence [156] Secondary: sun protection behavior [157]	Number of sunburns Percentage of sun exposure days using sun protection
HPV^b^ vaccination	Primary: any dose of HPV vaccine [158] Secondary: completion of vaccine series	Received 1 or more doses Received 2 or 3 doses as recommended for age

^a^MVPA: moderate to vigorous physical activity.

^b^HPV: human papillomavirus.

Self-report measures are most practical for this pragmatic trial, with the large sample of emerging adults in 4 geographically large states (approximately 1,100,700 sq km), web-based recruitment, and a multirisk factor approach that makes clinical and observational measures infeasible. The recall period for nicotine abstinence, alcohol use, and sunburn prevalence measures will be 30 days, which improves reliability [156]. Physical activity and other meal behaviors will be measured for the past 7 days, and HPV vaccination will be measured from baseline.

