### Statistical Analysis Plan

#### Hypothesis Testing

We plan to use advanced statistical methods suitable for stepped-wedge designs to compare outcomes between different cohorts and time points, which will account for both time effects and intervention effects. This includes using mixed-effects models or generalized estimating equations that can adjust for time-related trends and cohort effects. In addition, by comparing cohorts that start the intervention at different times, we will isolate the effect of our campaign from other external factors and assess whether changes in the cancer risk behaviors are more pronounced or accelerated following the introduction of our intervention compared with the periods before the intervention. In addition, our analysis will adjust for potential confounding factors that might influence cancer risk behaviors, such as age, sex, ethnicity, and other relevant sociodemographic factors. This approach ensures that the control aspects of the design are rigorously analyzed.

Specifically, the 2 hypotheses and exploratory research questions will be tested using R (R Foundation for Statistical Computing) [179] and Mplus, V8.2 (Munthén & Munthén) [180], a structural equation modeling program that allows for growth models and latent constructs (to model measurement error appropriately), repeated measures, direct and indirect effects, and moderators using interaction terms and multiple group analysis [181]. Mplus will handle missing data via full information maximum likelihood. All tests will be intent to treat. To mitigate false discovery (type I error), an α of .008 will be used (ie, the traditional α=.05÷6 [number of cancer risk factors considered]) [182]. Once the full sample is recruited, baseline data will be described and plotted, measurement models will be assessed, and transformations for normality will be examined and applied.

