The effect of the treatment on each of the primary outcomes will be examined using a linear mixed-effects model for a stepped-wedge design, as outlined by Hussey and Hughes [183] and Li et al [184]. Repeated measures (6 per individual—T_0_, T_1_, T_2_, T_3_, T_4_, and T_5_ in Figure 1) will be regressed on time since the start of the study (“calendar time”) and time since the start of message exposure (“exposure time”), both of which are expressed as categorical variables via dummy codes. Any mediators found to be significantly impacted by the treatment will be subsequently examined as mediators of the treatment effect on the outcomes via formal mediation models. Multilevel mediation models will be fit as described by Preacher [185] using the structural equation modeling program. As moderation tests require a vastly larger sample than tests of main effects [186], we will examine them without conducting null hypothesis significance tests [187]. We will estimate each model, evaluate the effect magnitude as a function of the moderator, construct bootstrap CIs to illustrate uncertainty, and use false discovery rate controls [182,187]. Linear mixed-effects models for hypothesis 1 will be extended to consider effect modification because of cancer risk behaviors, campaign exposure variables, biological sex, and the time of year of data collection (to control for seasonal fluctuations in UV levels, food availability, and alcohol intake).

Finally, behavioral and experiential engagement will be tested for campaign dose response (ie, duration of the campaign) related to cancer risk behaviors. In addition, behavioral engagement with posts (ie, views, reactions, and comments) on certain topics (eg, risk behaviors, media literacy, or family communication) and formats (eg, text, video, or interactive features such as polls) will be examined to determine if they have an impact on campaign effectiveness.

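### The linear mixed model planned for the 30-day sunburn count does not hold its .008 level in its usual form, because the count's variance follows the season and neither the transformation nor the time-of-year term corrects for that

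*Protocol article*

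**What the plan says.** All references are to the protocol article.

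- **Model (Hypothesis Testing).** "The effect of the treatment on each of the primary outcomes will be examined using a linear mixed-effects model for a stepped-wedge design". Calendar time and exposure time enter as fixed effects, "both of which are expressed as categorical variables via dummy codes".
- **Non-normality (Hypothesis Testing).** Once recruitment is complete, baseline data are to be plotted and "transformations for normality will be examined and applied".
- **Other methods (Hypothesis Testing).** The opening paragraph speaks of "using mixed-effects models or generalized estimating equations that can adjust for time-related trends and cohort effects", without linking either method to an outcome.
- **Season (Hypothesis Testing).** Time of year is listed among the effect modifiers, "to control for seasonal fluctuations in UV levels, food availability, and alcohol intake".
- **Level (Hypothesis Testing).** For six risk factors, "an α of .008 will be used".
- **Outcome (Table 1).** The primary UV measure is labelled a prevalence, but its metric is "Number of sunburns". The text below the table sets a 30-day recall.
- **Timing (Randomized Stepped-Wedge Trial Design).** Assessments fall at baseline and weeks 13, 26, 39, 52 and 104, and the four cohorts start 13 weeks apart. T0, T4 and T5 therefore share a season, and T2 falls in the opposite one.

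**The concern.** With 30-day recall and quarterly waves, each assessment samples one season. Calendar-time dummies, and a time-of-year term if added, remove the seasonal shift in the mean. They leave the seasonal shift in the variance, and for a count the variance moves with the mean. A model with one residual variance credits every wave with the average variance.

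The waves do not contribute equally to the campaign effect. At T0 nobody is exposed and at T4 and T5 everyone is, so a single exposed/unexposed contrast comes mainly from T1 to T3. With exposure-time dummies T4 also contributes, because the cohorts then have 13 to 52 weeks of exposure. If the waves that carry the contrast are the sunny ones, the reported standard error is too small; if they are the dark ones, it is too large.

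The .008 level protects the six-outcome family only if each test holds it. For sunburn, the calendar month of baseline could decide whether the test over-rejects or can hardly reject at all.

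**Working it through.** **1. The plan's level.** .05/6 = .00833, used as .008. Two-sided (the article does not state sidedness), the critical value is z = 2.652.

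**2. Assumed inputs.** The article gives no sunburn mean, variance, seasonal ratio or baseline month, so these are illustrative:
- mean 30-day sunburns in winter/spring/summer/autumn of 0.05/0.25/0.50/0.20 (mid) or 0.10/0.20/0.35/0.15 (mild);
- gamma person frailty with variance 1.5 and occasion overdispersion 0.5;
- 175 per cohort, from the article's 250 × 0.7. The ratio of standard errors below does not depend on n.

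Then Var(Y) = μ + μ²[(1 + 1.5)(1 + 0.5) − 1] = μ + 2.75μ², and Cov(Yj, Yk) = 1.5 μj μk.

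**3. Variance by season.**
- Mid: winter 0.05 + 2.75 × 0.0025 = 0.0569; summer 0.50 + 2.75 × 0.25 = 1.1875. The ratio is about 21.
- Mild: winter 0.1275, summer 0.6869. The ratio is about 5.4.

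**4. What the usual fit assumes.** Mid rates, winter baseline, T0-T4: the wave variances are 0.0569, 0.4219, 1.1875, 0.3100 and 0.0569, with average 2.0332/5 = 0.4066. The means sum to 1.05 and their squares to 0.3575, so the average covariance is 1.5 × (1.05² − 0.3575)/20 = 0.0559. The fitted matrix W has 0.4066 on the diagonal and 0.0559 elsewhere. The true matrix V keeps the unequal values.

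**5. Reported and true standard error.** With A = Σ n X′W⁻¹X over the four cohorts, the model reports A⁻¹. The true variance is A⁻¹(Σ n X′W⁻¹VW⁻¹X)A⁻¹. True size = 2Φ(−2.652 × SE reported/SE true). Exposure time has four levels (13, 26, 39 and 52 weeks). Where T5 is used, each cohort keeps its week-52 level.

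Average of the exposure-time dummies, mid rates:
- winter, T0-T4: 0.0392/0.0453 = 0.864, so 2Φ(−2.29) = 2.2%;
- winter, with T5: 0.0345/0.0449 = 0.769, so 2Φ(−2.04) = 4.1%;
- summer, T0-T4: 0.0498/0.0408 = 1.222, so 2Φ(−3.24) = 0.12%.

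Single campaign indicator, winter, T0-T4: 0.0312/0.0423 = 0.738, so 2Φ(−1.96) = 5.0%.

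**6. All cases** (mid and mild rates, with and without T5; nominal 0.8%):

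| Baseline season | Average of exposure-time dummies | Single campaign indicator |
|---|---|---|
| Winter | 1.5-4.1% | 3.2-7.2% |
| Autumn | 2.1-2.7% | 1.5-1.8% |
| Spring | 0.2-0.4% | 0.8-0.9% |
| Summer | 0.03-0.24% | 0.004-0.03% |

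**7. Check with other assumptions.** A separate derivation and simulation used a sinusoidal season, summer means of 0.4-1.0, winter means of 0.05-0.15, 250 per cohort and 30% monotone dropout.
- Exposure-time average, raw counts: winter about 2.0-4.8%, summer 0.0-0.4%. The two intermediate seasons gave 0.5-2.9% in simulation, so the spring figure depends on the shape of the seasonal curve.
- After log(1+y): winter 1.7-4.2%. Scored as any sunburn yes/no: winter 1.9-2.9% in simulation.
- Joint 4-df test of the dummies: about 0.2-3.3%, with no clean winter/summer split.
- No seasonality: 0.6-0.7%. Season is therefore the cause.
- Participant-level sandwich variance: about 0.4-1.3% in every baseline season, for raw, log and yes/no coding.

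**8. Power in the conservative direction.** With a summer baseline and a single campaign effect, simulated power for 30% fewer sunburns was 2-8% with model-based standard errors and 28-30% with robust ones.

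**The case against.** The strongest reply is that the error lies in details the article never states. It does not say one residual variance, compound symmetry or model-based standard errors, and those belong in an analysis plan that is not shown. The Results section says a subcommittee for statistical analysis is still to be formed. The structural equation software it names can also fit wave-specific variances. This stands in part: the finding is conditional on the usual form of the model. It does not dispose of the point, because the article does state a model and a remedy for non-normality, and that remedy and the seasonal term both miss the variance.

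A reader might infer three stronger claims that the document does not support.

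- **That a transformation is the only safeguard.** Estimating equations are named, and with a robust variance they would restore the level. They are assigned to no outcome, and the next paragraphs give every primary outcome to the linear mixed model. This is a tension to resolve, not an absent method.
- **That the planned test runs at 3-7%.** That range belongs to a single campaign indicator with a winter baseline. The article specifies exposure-time dummies, whose average gives about 1.5-5%. The power section's target, a time-averaged effect, makes a single summary relevant but does not change the model stated.
- **That transforming sunburn must be ruled out.** With robust standard errors the test holds its level on the raw, log and yes/no scales alike, so only the variance estimator needs to change.

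It might also be said that recruitment over several months blurs the seasons. Spreading enrolment over three months (log scale, summer baseline) still gave 0.07% for the single indicator and 0.33% for the exposure-time average.

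**Conclusion.** The concern holds in conditional form. A linear mixed model with a random intercept, one residual variance and model-based standard errors does not deliver a .008 test for a 30-day sunburn count.

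For the average of the exposure-time dummies, the true level is about 1.5-5% with a winter baseline, about 2-3% with autumn, and about 0.4% or less with spring or summer. Even the mildest winter case nearly doubles the nominal level, and the highest summer figure in the table is less than a third of it. A single indicator is more extreme in winter and summer and close to nominal in spring.

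The direction follows from the wave timing and the link between mean and variance in a count. The size rests on assumed seasonal rates, overdispersion and baseline month, none of which the article supplies, and the spring figure is the least certain. The point concerns the standard error and test for sunburn, not the effect size in the power section.

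**What to change.** In Hypothesis Testing, where the mixed model is specified, state that the standard error and test of the campaign effect on sunburn use a participant-level robust (sandwich) covariance or a participant bootstrap, or that residual variances may differ by wave. Apply this whether sunburn is raw, transformed or yes/no, and use the same approach by default for the other primary outcomes.

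Two passages should be reconciled with it:
- the opening reference to estimating equations, by saying which outcomes, if any, they apply to;
- Table 1, where the measure is called a prevalence and the metric is a number, by saying which is primary.

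A log-link count model is optional. It targets a rate ratio, not a mean difference. Fitted by estimating equations, it would also give up the full-information likelihood handling of incomplete cases that the article relies on with 30% planned dropout.

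**Cost:** plan wording and a software option, with no new data. The sunburn interval becomes wider when baseline falls in winter or autumn.

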**Figure 1 figure1:**
[figure not shown]
Randomized stepped-wedge trial design.

Following baseline assessment (T_0_), emerging adults will be stratified by state, ethnicity (racial and ethnic minority individuals vs non-Hispanic White individuals), and biological sex (male vs female) and randomly assigned to 1 of 4 cohorts differing in intervention duration by the project biostatistician. All cohorts will complete postintervention assessments at weeks 13 (T_1_), 26 (T_2_), 39 (T_3_), 52 (T_4_), and 104 (T_5_). All data collection will be conducted using the secure web-based REDCap (Research Electronic Data Capture; Vanderbilt University) application. The primary outcomes measured at all assessment times will be MVPA, healthy eating patterns, nicotine product use, alcohol intake, sunburn, and HPV vaccination.

The social media campaign will be conducted over 12 months in 4 separate Facebook private groups. The intervention will start in each cohort at successive 13-week intervals, so cohorts will receive varying doses of campaign exposure (ie, 180 posts per 13-week interval) via stepped entry. Specifically, cohort 1 (250/1000, 25%) will start the social media campaign at week 1, receiving approximately 720 posts in 52 weeks. Cohort 2 (250/1000, 25%) will start the campaign at week 13 (approximately 540 posts), cohort 3 (250/1000, 25%) at week 26 (approximately 360 posts), and cohort 4 (250/1000, 25%) at week 39 (approximately 180 posts). Emerging adults will be told to read, react to, and comment on posts as often as they like. Exposure to cancer risk information and misinformation from other sources will be controlled by randomization.

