
#### Development of Cancer Prevention Posts

An agile, just-in-time process will be used to create and adapt posts to be responsive to emerging adults and to reflect current events [133]. Investigators will prepare a campaign framework for developing posts, identifying target behaviors for each cancer risk factor and key theoretical principles. Project staff will continuously audit cancer prevention information and misinformation in (1) published literature, government reports, and national surveys; (2) participant comments on posts; (3) quarterly web-based emerging adult focus groups; and (4) advisory board input. The investigators and media developers will revise posts, add emerging themes, and tailor posts to key subgroups. Initially, 3 months of campaign posts will be prepared, with additional posts developed during the campaign, creating a planned adaptive campaign. Social media posts will be written in English because rural emerging adults are the primary target group, with Hispanic and American Indian emerging adults comprising a minority of them. English continues to be the most common language on the internet, especially in the United States [134,135]. Nearly all young adults in the United States are proficient in English, even most foreign-born young adults [136].

To ensure campaign exposure, posts must regularly engage users because the Facebook algorithm presents posts from the private groups more frequently and prominently in participants’ newsfeeds when they engage more with the group’s posts. To achieve high visibility and engagement, we will post twice per day and (1) provide novel, high-interest, useful, and current-event content; (2) adjust for season; (3) link to content from other emerging adults to create descriptive norms; (4) address age differences and cultural barriers and facilitators; (5) use ethnically diverse emerging adult images that can improve health communication [137]; and (6) use formats such as stories, polls, questions and answers, videos, and visuals, and invite comments [58,98,138-141].

The campaign will be pilot-tested with rural emerging adults (N=25) meeting the inclusion and exclusion criteria displayed in Textbox 1 (13/25, 52% female individuals and ethnically diverse). It will contain a feed of 56 campaign posts (2 per day) over 4 weeks, and participants will provide feedback in focus group discussions.

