#### Social Media Campaign Engagement Measures

Behavioral and experiential measures of campaign engagement [174,175] will be collected, guided by the model of engagement by Perski et al [176]. Behavioral measures will be (1) staff records of posts; (2) counts of emerging adults’ views, reactions (eg, like or sad), and comments extracted in identified format using our custom-written app and coded for content and pro, anti, or neutral sentiment by 2 trained research assistants [113]; and (3) use of resources on the project website recorded by the web server. Experiential measures will be collected in each postintervention test, including time spent and frequency of reading posts, flow experience (ie, social interaction, enjoyment, and concentration) [177], cancer information overload [178], and sharing post content with others.

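### The plan treats self-selected engagement, alongside randomised campaign duration, as dose response, so the exploratory engagement, topic and format results can be confounded by motivation

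*Protocol article*

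**What the plan says.** All references are to the protocol article.

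- **Hypothesis Testing**, on dose: "behavioral and experiential engagement will be tested for campaign dose response", followed by a parenthesis that equates dose with how long the campaign runs.
- **Hypothesis Testing**, next sentence, on views, reactions and comments by topic and format: these "will be examined to determine if they have an impact on campaign effectiveness".
- **Randomized Stepped-Wedge Trial Design**: participants are "randomly assigned to 1 of 4 cohorts differing in intervention duration". On engagement: "Emerging adults will be told to read, react to, and comment on posts as often as they like".
- **Development of Cancer Prevention Posts**: "the Facebook algorithm presents posts from the private groups more frequently and prominently" to participants who engage more with the group.
- **Social Media Campaign Engagement Measures**: "Experiential measures will be collected in each postintervention test", so self-reported engagement comes from the same follow-up surveys as the outcomes.
- **Strengths and Limitations**: the design and the engagement analysis are together meant to assess campaign dose effects. Engagement measures are also meant to give insight into which strategies affect outcomes. The same passage describes the topic and format work as an association with behaviour change.
- **Mediators** and **Potential Covariates**: motivation is measured in every survey, but it is listed as a mediator and is not on the covariate list.
- **Objectives**: the engagement question is exploratory.

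**The concern.** Two different quantities share one name. Assigned duration is set by randomisation, so comparing outcomes across durations compares like with like. Engagement is chosen by the participant once the campaign is running and is then reinforced by the platform. It is also undefined in the control periods. A person already inclined to improve diet or activity is plausibly also the person who reads and comments more. A slope of behaviour on engagement then mixes any campaign effect with that inclination.

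The conclusions at stake are which dose, topics and formats work. These would guide later campaigns. Calling the analysis exploratory limits the weight placed on it, but does not remove bias from the estimate or its confidence interval. A test by achieved engagement is also hard to square with the section's statement that every test follows intention to treat.

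**Working it through.** The plan gives no figure for this analysis, so there is none to reproduce. The check asks how large a slope can arise when engagement has no effect.

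**Inputs from the protocol.** Four cohorts of 250; within-person correlation 0.5; α = .008; planned standardised effect 0.2; about 175 completers per cohort (700 in total).

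**Assumptions.** Five waves, T0 to T4. Total variance 1, so person variance and residual variance are 0.5 each. The test is two-sided (critical value 2.652), since sidedness is not stated. Engagement E is standardised and correlates ρ = 0.1, 0.2 or 0.3 with the stable person effect. The true engagement slope is zero. The values of ρ are not from the protocol.

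**Step 1: comparison among exposed people only.** The spurious slope is ρ × √0.5, which gives 0.07, 0.14 and 0.21 SD per SD of engagement. The last is as large as the planned effect.

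**Step 2: mixed model with an engagement-by-exposure term and no engagement main effect.**

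- The person effect contributes ρ√0.5·E at every wave. The expected slope is ρ√0.5 × Σ x′V⁻¹1 / Σ x′V⁻¹x, summed over cohorts, where x is a cohort's exposure indicator.
- With V = 0.5(I + J), V⁻¹ = 2(I − J/6). For a cohort exposed at s waves, x′V⁻¹1 = s/3 and x′V⁻¹x = 2(s − s²/6).
- For s = 4, 3, 2, 1 the sums are 10/3 and 2(10 − 30/6) = 10, so the ratio is 1/3.
- Slope = 0.707ρ/3 = 0.236ρ.
- Standard error with 250 per cohort = 1/√(250 × 10) = 0.020. With 175 per cohort it is 1/√(175 × 10) = 0.024.

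| ρ | Slope (formula) | Slope (300 simulated trials) | False positives at .008, N=1000 (formula) | Same, simulated | Formula, N=700 |
|---|---|---|---|---|---|
| 0.1 | 0.024 | 0.024 | 7% | 8% | 5% |
| 0.2 | 0.047 | 0.045 | 38% | 34% | 25% |
| 0.3 | 0.071 | 0.070 | 81% | 81% | 62% |

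The slopes are 12% to 35% of the planned 0.2 (0.024/0.2 and 0.07/0.2).

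**Step 3: the same model with the engagement main effect added.** The term ρ√0.5·E is constant over waves, so the main effect absorbs it. In simulation the interaction slope is about zero and the error rate is near nominal.

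**Step 4: motivation that drives change.** The main effect does not help here. Let motivation correlate a with engagement and b with outcome change, and set the campaign effect to zero. Regress change on engagement and assigned duration. The engagement slope is a × b and its standard error is about 1/√N (0.038 for N = 700). Results from 2,000 simulated trials per setting:

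| a, b | Slope | Engagement false positives at .008, N=700 | N=1000 |
|---|---|---|---|
| 0.2, 0.2 | 0.04 | 5.7% | 9% |
| 0.3, 0.3 | 0.09 | 39% | 58% |
| 0.5, 0.3 | 0.15 | 90% | 98.5% |

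With a = 0 the rate stays at 0.7% to 1.3%. The test of randomised duration stays at 0.5% to 1.1% in every setting.

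**The case against.** The strongest reply is that the protocol's own gloss defines dose as campaign duration, which is randomised. Comparisons of assigned duration are already planned in Randomized Stepped-Wedge Trial Design and in Cancer Prevention Social Media Campaign, and exposure time is in the main model. This largely stands: a reader might infer that the plan neglects its randomised dose, and the text does not support that. However, the sentence's subject is engagement, so the gloss joins the two quantities. The topic and format sentence carries no duration qualifier.

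Other points for the plan:

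- **Wording.** Strengths and Limitations already speaks of association for topic and format, and Hypothesis Testing poses effectiveness as a question to examine. This stands in part, because the same Discussion section keeps the causal aim.
- **Model form.** The protocol never states an interaction model without its main effect, and an interaction is normally fitted with its main effects. This stands: Step 2 shows what happens if the main effect is left out, not what the plan prescribes.
- **Testing.** Moderation, including by campaign exposure variables, is to be estimated without significance tests. This stands for those analyses, although the dose-response sentence says engagement will be tested. A biased estimate also biases its interval.
- **Adjustment.** The candidate covariates go beyond demographics to prior preventive care, exposure to cancer information and social desirability. This stands, but motivation is not among them.
- **Direction.** If people with more risk behaviours engage more, the bias could run the other way. This stands.

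**Conclusion.** The concern holds for the exploratory engagement, topic and format analyses. As worded, the plan can attribute to engagement a difference that comes from who engages. Under the assumed correlations of 0.1 to 0.3 and without the engagement main effect, the spurious slope is about 0.02 to 0.07 SD per SD, with false positives of about 8% to 81% at .008 (1,000 participants). With the main effect, bias from stable differences is about zero. Bias from motivation to change remains and equals a × b under the Step 4 model.

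Two stronger readings are not supported. One is that these results are bound to be positive: that depends on the sign and size of correlations the protocol does not give, and on model terms it does not state. The other is that the trial's main result is compromised: the primary model rests on assigned cohort, calendar time and exposure time, and the randomised-duration test stayed near nominal throughout.

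**What to change.** In Hypothesis Testing:

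1. Reserve the term dose response for assigned duration, using the between-cohort comparison already planned, and describe engagement in a separate sentence.
2. In engagement models, include each person's overall engagement as a main effect alongside its interaction with exposure. Adjust for baseline motivation and baseline behaviour, both already collected at T0.
3. Report engagement, topic and format results as associations, matching the word already used in Strengths and Limitations, and do not present them as impact on effectiveness. Adjustment for measured motivation cannot rule out motivation that changes during follow-up, so this label is needed even after step 2. Align the remaining sentences in Strengths and Limitations.

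Using cohort assignment as an instrument for posts viewed is not a safe substitute. Assignment may also act through the resource website, live events and comments, so an effect through views alone cannot be assumed.

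The cost is slightly more analysis and weaker claims about which strategies work. No new data or change to the trial's conduct is needed.
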